### Sample size

In the database used to validate the FQoR-15 questionnaire, 21 patients were operated on for cardiac surgery with sternotomy, and the average FQoR-15 score was 90 ± 18. The minimal important difference of the QoR-15 score is usually set at 8.0 [26].

We assume that the DPIP has a greater impact than the SPIP on QoR, and we set mean QoR-15 values of 98 in the SPIP group and 106 in the DPIP group.

The management of comparisons and the type I error risk will be performed in a sequential hierarchical strategy (Fig. 3). First, we will compare the primary endpoint (QoR-15 value at H24) between the interventional groups (patients in the SPIP and DPIP groups combined) with the standard group. If efficacy is revealed by this first comparison, further comparisons will be performed between the SPIP and DPIP groups only. Considering a type I error risk of 0.05 in a two-sided test and a statistical power of 0.8, 80 patients will be needed in each intervention group (i.e., SPIP and DPIP) to obtain the minimum power to conclude on the comparison between both groups. With 80 patients in the standard group, we expect to achieve greater than 95% power in the first analysis of the primary outcome (interventional groups versus standard group). Considering our three groups (SPIP, DPIP, and standard groups) and assuming a maximum rate of 5% of patients for whom the primary endpoint will not be available, we plan to include 254 randomized patients.

**Fig. 3 Fig3:**
[figure not shown]
Diagram of the hierarchical classification of the statistical tests (type I error management). Abbreviations: Deep PIP, deep parasternal intercostal plane block; FQoR-15, French version of the QoR-15; H24/48/72, 24/48/72 h at surgery; PNB, peripheral nerve block; Superficial PIP, superficial parasternal intercostal plane block

### Follow-up

Day 0 (D0) is the day of surgery with hour 0 (H0) corresponding to the time of randomization. The delay between randomization, achievement of the intervention for the arms with PNB, and admission to the ICU will be negligible (a few minutes). Ten visits are scheduled after the inclusion, and the summarized plan is presented in Fig. 1. The follow-up will begin at the pre-inclusion visit during the anesthesia consultation aiming to collect demographic data, type of surgery, medical history, vitals parameters (cardiac rate and blood pressure), and the pre-operative QoR-15 score.

The inclusion visit will be realized at the end of the surgery during the skin closure. Once the patient is included and allocated to one arm, the block will be carried out according to the allocation group before the transfer to the ICU. The operator’s satisfaction will be assessed on a Likert scale at this time. Perioperative surgical and anesthesia data will be recorded.

On ICU admission, the collected data will be the hemodynamic parameters, the biological values, and a local or systemic complication possibly linked to block. The intensity of pain at rest and during effort, the consumption of analgesics, and the notification of local or systemic complications will be collected during the following visits at 3, 6, 12, 24, 48, and 72 h after the surgery. The QoR-15 questionnaire will be completed at H48 and H72. At H24, patients will detail the body localization of the most intense pain, the use of a rescue peripheral nerve block, and the intensity of pain at the removal of the pericardial drains. Morphine equivalents and non-opioid analgesic drugs consumptions will be collected at 4 and 5 days after the surgery. The patient’s weight and the occurrence of bowel movement will be noted at H72 and 5 days after the surgery.

Thirty days after the surgery, the following data will be collected: a puncture site or a postoperative complication, the length of hospital censored at D30 if the patient is still hospitalized, and length of stay in ICU. Potential readmission to ICU will also be notified. If the patient’s condition does not allow him to be contacted directly or by phone, the person in charge of the follow-up will be contacted (e.g., family member or physician).

### Safety

The major potential adverse effects linked to SPIP and DPIP are pneumothorax, mediastinitis, hematoma, puncture site infection, and intoxication with ropivacaine [27–29]. Continuous monitoring of vital parameters within 3 h following the PNB procedure will be carried out to detect local anesthetic toxicity. A chest X-ray is systematically realized at ICU admission, and this investigation will allow to detect the presence of a pneumothorax. The body temperature will be noted every 3 h by a nurse, and the monitoring of the occurrence of complications at the puncture site will be done at each visit up to D30. The occurrence of a serious adverse event will be collected at any time during the patient’s follow-up (up to 30 days), whose imputability with one of the allocation groups will be discussed.

### Data collection and study monitoring

The information will be recorded in the electronic web-based case report form (Ennov Clinical® eCRF) managed by the clinical research team of the Angers University Hospital.

A clinical research associate (CRA) mandated by the study sponsor will ensure the successful completion of the study, the data collection, documentation, recording, and report, in accordance with the Standard Operating Procedures implemented in the Angers University Hospital and in accordance with good clinical practice, laws, and regulations.

Different items will be reviewed for every fifteen included patients: signed informed consent, compliance with procedures, and quality of collected data. An automated data check will be made by the data management team based on the data validation plan signed by the coordinating investigator. Detected errors will lead to the issuance of requests for information and electronic correction. Given the low risks associated with this study, which consists of comparing two treatments already used routinely, an independent monitoring committee will not be set up for this study.

The promoter can notify any deviation from the protocol using a breach report form.

### Type I error management

The management of the type I error will be done in a sequential hierarchical manner. A representative diagram of the hierarchical decision is presented in Fig. 3. As long as the *p*-value is less than 0.05, the comparisons will be continued for conclusion. If for any of the comparisons the *p*-value is superior to 0.05, the comparisons will only be made for exploratory purposes and will be delivered explicitly as such. The hierarchical list of comparisons will be made first on the primary outcome (QoR-15 at H24) between the interventional groups and the standard group. The rest of the comparisons will be done between the SPIP versus DPIP groups on the primary endpoint and then on several secondary endpoints. Comparisons on other outcomes (not shown in the diagram) will be exploratory.

### Statistical analysis

All analyses will be performed using the R software (version 4.1.3). The main analysis will be in intention-to-treat, including all randomized patients. Patients will be analyzed according to their randomization group. A per-protocol analysis will be performed as a sensitivity analysis to assess the main robustness analysis. A flow chart of all patients (Fig. 2) and descriptive statistics will be used to describe baseline characteristics. Data will be presented by their mean with standard deviation, median with interquartile range, according to their normal or non-normal distribution respectively, and number with the percentage of sample (%). For the endpoint comparisons, we will report both absolute measures (differences in means or percentages) and relative measures (odds ratios or hazard ratios), with their 95% confidence interval.

We will detail the missing data on the endpoints involved in the type I error hierarchical management only. We will identify the status of these missing data for these criteria between completely randomly missing, randomly missing, or non-randomly missing. For criteria with less than 10% missing data, we will not perform a missing data management method. For criteria with more than 10% missing data on these criteria, we will perform sequential multiple imputations by chained equations (mice package in R, with 5 imputations, from predictors/variables at inclusion, set.seed 1111). If the multiple imputation method is used (i.e., more than 10% missing data), we will study the impact of the data imputation. We will then carry out an analysis of the concrete cases, as well as the following sensitivity analyses: “best–worst” and “worst-best.” For the “best–worst” scenario, it is assumed that all patients lost to follow-up will have a beneficial outcome, whereas in the “worst-best” scenario, they will have a negative outcome. For the continuous outcomes, the beneficial outcome will be the mean value of the group plus one standard deviation, while the adverse outcome will be the mean minus one standard deviation.

For all analyses using regression models, the included covariates will be the allocation group, as well as the stratification group (surgery with or without thoracic internal arterial graft). For analyses requiring a mixed model, the covariates introduced will be a fixed effect for the treatment arm, a fixed effect for the stratification factor, a fixed effect for the time frame of the visit, and a random effect for the patients, and under an unstructured variance/covariance matrix. If the mixed models do not converge, we will use a compound symmetry correlation structure. To address the main objective, we will use a linear regression model. Similarly, the QoR-15 score at H48 will be analyzed using a linear regression model. The evolution of effort pain up to H48 will be analyzed using a linear mixed model. The evolution of morphine equivalent consumption will be analyzed using a mixed model, following a Poisson distribution. The rate of occurrence of at least one postoperative complication will be compared by logistic regression. Censored 30-day hospital stay will be assessed by survival analysis using a semi-parametric Cox model.

The other endpoints will not have a method of imputation for missing data. Thus, only those individuals for whom endpoints are available will be included in the analyses. These data will be analyzed for exploratory purposes. The evolution of pain at rest will be analyzed with a linear mixed model, and we will compare the evolution of the consumption of non-opioid analgesic drugs with a mixed model, following a Poisson distribution. The proportions of patients with pain at H24 and H48, as the rate of local and systemic complications during the follow-up will be compared using logistic regression. The total hospital consumption of morphine equivalent in the first 72 h will be assessed by Poisson regression. Pain intensity at the pericardiac drain removal at H24 will be assessed by linear regression. Time to resuscitation censored at 30 days, time to extubation, time to recover bowel movements, and time to return to preoperative weight will be assessed by survival analysis using a semi-parametric Cox model. The distribution of postoperative complications will be compared by multinomial regression. Satisfaction with the block procedure and the main painful area at H24 will be presented descriptively in the groups.

All tests will be two-sided. Statistical significance is set in the usual way with a *p*-value < 0.05, and 95% confidence intervals will be estimated for each calculated value. For the primary endpoint (QoR-15 score at H24), a sensitivity analysis will be performed without including the stratification factor in the model.

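### The primary endpoint's missing-data checks run only above 10% missing, while the plan expects at most 5%; as worded, the best–worst scenarios also barely test the group difference

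*Protocol article*

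**What the plan says.** All references are to the protocol article.

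- **Population** (Statistical analysis): "The main analysis will be in intention-to-treat, including all randomized patients".
- **Below 10% missing**, for endpoints in the testing hierarchy: "For criteria with less than 10% missing data, we will not perform a missing data management method".
- **Above 10%**: "For criteria with more than 10% missing data on these criteria, we will perform sequential multiple imputations by chained equations", with 5 imputations drawn "from predictors/variables at inclusion, set.seed 1111".
- **Sensitivity analyses for missing data**: "If the multiple imputation method is used (i.e., more than 10% missing data), we will study the impact of the data imputation". The observed-case, best–worst and worst–best analyses follow from that condition. Best–worst gives a good outcome to all patients lost to follow-up, and worst–best gives all of them a poor one. For continuous outcomes, "the beneficial outcome will be the mean value of the group plus one standard deviation"; the poor outcome is the mean minus one SD.
- **Expected missingness** (Sample size): the total is inflated "assuming a maximum rate of 5% of patients for whom the primary endpoint will not be available".
- **Primary model** (Statistical analysis): linear regression of the single 24 h score on allocation and the stratification factor.

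The same section also commits, at any missing rate, to describing the missing data on hierarchical endpoints and classifying them as completely random, random or non-random.

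**The concern.** A linear regression on one time point cannot use a patient who has no score at that time. With no missing-data method applied, the primary analysis is a complete-case analysis. The plan's own ceiling of 5% puts the trial well inside the range where every missing-data check is switched off.

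The trigger is a percentage alone. If the planned classification concluded that the missing scores were non-random, nothing further would be run below 10%.

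This matters because the score is self-completed on paper in intensive care at 24 h. Failure to complete it could plausibly be related to recovery itself. The documents do not say who will be missing, so this is an inference from the design. The SPIP–DPIP comparison at 24 h is also the second step of the hierarchy (Type I error management), so all later confirmatory tests depend on it.

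The scenarios have a separate weakness even when they are triggered. Moving all lost patients the same way puts little stress on a between-group difference.

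**Working it through.** **Inputs.** SD 18, means of 90 (standard), 98 (SPIP) and 106 (DPIP), 80 evaluable per group, 254 randomized, at most 5% missing (Sample size); scenario values of mean ±1 SD and a 10% trigger (Statistical analysis). Equal missingness across arms and a common SD of 18 are assumptions.

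**1. The plan's own figures.** n per group = 2 × (1.96 + 0.842)² × 18² / 8² = 79.5, so 80, as stated. 240 / 0.95 = 252.6, so 253, or 3 × 85 = 255 if each arm is rounded up. The stated 254 lies between these. The sample size is sound and already allows for 5% loss.

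**2. Which rule applies.** 5% of 254 is 12.7, about 13 patients. The trigger needs more than 10%: 25/254 = 9.8% does not reach it and 26/254 = 10.2% does. So up to 25 patients can be missing with no check. Exactly 10% is covered by neither rule.

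**3. Scenarios as worded.** With a fraction d missing in each arm, each arm mean moves by d × 18 in the same direction. Change in the difference = d × 18 − d × 18 = 0. With unequal fractions it is (d1 − d2) × 18. For example, 2% against 8% gives 0.06 × 18 = 1.1 points.

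**4. Scenarios opposed by arm.** Change in the difference = 2 × d × 18.

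| Missing | Change | SPIP–DPIP, planned 8 | Blocks–standard, planned 12 |
|---|---|---|---|
| 5% | ±1.8 | 6.2 to 9.8 | 10.2 to 13.8 |
| 25/254 = 9.8% | ±3.5 | 4.5 to 11.5 | 8.5 to 15.5 |

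**5. Comparison with the significance threshold.** For SPIP–DPIP at 80 per group, SE = 18 × √(2/80) = 2.85, so the smallest significant difference is 1.96 × 2.85 = 5.6. With all 254/3 = 84.7 per group filled in, it is 5.4. For blocks against standard, SE = 18 × √(1/80 + 1/160) = 2.46, and the threshold is 4.8.

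At 5% missing, an observed SPIP–DPIP difference of 8 stays above the threshold (6.2). An observed difference between 5.6 and 5.6 + 1.8 = 7.4 would be significant but fall below 5.6 in the adverse scenario. Just under 10%, that band widens to 5.6 + 3.5 = 9.1 and includes the planned 8. The planned first-step difference stays above its threshold throughout.

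**The case against.** The best defence is that a complete-case analysis with few missing values is often acceptable, that the protocol openly expects some loss, and that it inflates the sample for it. The sentence following the intention-to-treat statement concerns analysis by allocated group, so the reference to all randomized patients is loose wording more than a hidden contradiction. This stands: a complete-case primary model can be kept. It does not explain why the robustness checks are off in the expected range.

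A reader might infer more than the documents support:

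- **That no sensitivity analysis is run below 10%.** The per-protocol analysis and the model without the stratification factor run regardless. Neither addresses missing outcomes, so only the missing-data checks are absent.
- **That nothing would reveal a problem.** Missing data on hierarchical endpoints are to be described and classified, and a flow chart is planned. That is disclosure, without an estimate of the effect on the result.
- **That missingness is known to be informative, with a known bias.** No section says so. Participants excludes emergency, redo and septic cases, and confirms inclusion only in the absence of hemodynamic instability and of bleeding requiring immediate revision. Complete-case bias is (difference in missing fractions) × (gap between observed and missing patients). An assumed gap of 30 points with 2% missing in the block arms and 8% in control gives −1.8; a gap of 20 with 3% and 7% gives −0.8. Equal fractions and gaps give zero. Both examples understate the benefit of the blocks.
- **That imputation from inclusion variables merely returns the complete-case answer.** The primary model contains only allocation and stratum, whereas inclusion data are wider and the preoperative QoR-15 is collected beforehand. Such imputation can therefore add information, though it leaves out the scores recorded after surgery.

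The label best–worst may suggest that the arms were meant to move in opposite directions. The text does not say so.

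**Conclusion.** The point holds in limited form. At the missing rate the plan itself expects, the primary result is complete-case with no missing-data sensitivity analysis, whatever the classification of the missing values. The scenarios reserved for higher rates would, as worded, leave the difference almost unchanged when arms have similar missingness and SD.

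The untested movement in the SPIP–DPIP difference is about 1.8 points at 5% and 3.5 points just under 10%. These figures rest on SD 18, equal missingness and ±1 SD shifts in opposite directions; they are stress-test bounds, not estimates of bias. At 5% missing they threaten only results close to the threshold; near 10% they could reach the planned difference. Power is not the issue: for the second step it is about 0.80 at 5% missing and 0.78 just under 10%.

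**What to change.** Keep the complete-case regression as the primary analysis if wished, and describe it as such. Remove the 10% trigger for the primary endpoint's sensitivity analyses. At any missing rate, run:

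- **(a)** best–worst and worst–best scenarios with opposite directions in the compared arms. This addresses non-random missingness and changes the present rule.
- **(b)** multiple imputation with allocation, stratum, preoperative QoR-15, QoR-15 at 48 and 72 h, and the pain scores already collected. This assumes that missingness is random given those variables, so it complements (a) and does not replace it.

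The number of imputations is a minor choice. The cost is a wording change and a small amount of new analysis code. No new data are collected and the sample size is unchanged.

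### Imputing missed effort-pain scores from inclusion variables alone makes the standard error of the mixed-model arm effect too small once more than 10% are missing

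*Protocol article*

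**What the plan says.** All of this is in the Protocol article, Methods.

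- **Trigger.** Statistical analysis: "For criteria with more than 10% missing data on these criteria, we will perform sequential multiple imputations by chained equations". Below the threshold, "For criteria with less than 10% missing data, we will not perform a missing data management method".
- **Predictors and number.** The same paragraph fixes the method: "mice package in R, with 5 imputations, from predictors/variables at inclusion". It also fixes the random seed. No post-operative measurement is named as a predictor.
- **Back-up analyses.** If imputation is used, "We will then carry out an analysis of the concrete cases, as well as the following sensitivity analyses", namely best-worst and worst-best.
- **Which endpoints.** The rule covers the endpoints in the type I error hierarchy. The next part of the section names QoR-15 at H24 and H48, effort pain, morphine-equivalent consumption, complications and hospital stay, and then says that the remaining endpoints get no imputation. Pain at rest is among those remaining endpoints.
- **Model for effort pain.** "The evolution of effort pain up to H48 will be analyzed using a linear mixed model". The mixed models have fixed effects for arm, stratum and visit, with "a random effect for the patients, and under an unstructured variance/covariance matrix". No arm-by-visit term is listed, so the arm effect is an average over visits.
- **Visits.** Follow-up schedules pain scores at 3, 6, 12, 24, 48 and 72 hours, which is five visits up to H48.

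**The concern.** A patient's pain score at one visit says a good deal about the score at the next. If a missed visit is imputed from inclusion variables only, the imputed value is unrelated to that patient's observed scores, given those variables. The completed data then look less correlated within patients than the real data are. The variance of a visit-averaged arm effect rises with that correlation, so a diluted correlation gives a variance that is too small. Rubin's rules do not put the loss back.

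The step is also unnecessary. A linear mixed model fitted to the observed visits already uses each patient's other scores and is valid under missing at random. The plan applies imputation to confirmatory effort pain, while exploratory pain at rest keeps the mixed model on observed data.

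At stake is the effort-pain test of SPIP against DPIP, which appears to be one of the steps in a chain that continues only while p is below 0.05. A step whose real error rate exceeds 5% can be passed too easily, and so can lead on to later steps.

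**Working it through.** **Inputs from the protocol.** Five effort-pain visits up to H48 (Follow-up); two-sided 5% level and 80 patients per block arm (Sample size); imputation from inclusion variables with 5 imputations (Statistical analysis). The arm size reproduces: 2 × (1.96 + 0.8416)² × 18² / 8² = 79.5, so 80. The protocol gives no expected missing rate or within-patient correlation for effort pain.

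**Assumptions.** Equal correlation ρ between visits, 0.3 to 0.7; a fraction f of scores missing completely at random and independently by visit; arm included in the imputation model; many imputations.

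**Formulas.** With J visits, in units of σ²/n per arm:

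- True variance of the averaged estimate: [J/(1−f) + J(J−1)ρ] / J². Each visit mean rests on a fraction 1−f of the patients, and the covariance between two visit means stays at ρ.
- Variance reported by Rubin's rules: [J/(1−f) + J(J−1)ρ(1−f)²] / J². Two visits of a patient stay correlated in the completed data only when both were observed, which has probability (1−f)².

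The ratio of reported to true SE is the square root of the second over the first, and the type I error is 2 × [1 − Φ(1.96 × ratio)].

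**One case in full**, J = 5, ρ = 0.5, f = 0.20:

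- True: (6.25 + 10)/25 = 0.650
- Reported: (6.25 + 10 × 0.64)/25 = 0.506
- SE ratio: √(0.506/0.650) = 0.882
- Type I error: 2 × [1 − Φ(1.729)] = 8.4%

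**At other rates:**

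| f | ρ | J² × true | J² × reported | SE ratio | Type I error |
|---|---|---|---|---|---|
| 0.11 | 0.3 | 11.618 | 10.371 | 0.945 | 6.4% |
| 0.11 | 0.6 | 17.618 | 15.123 | 0.926 | 6.9% |
| 0.26 | 0.3 | 12.757 | 10.042 | 0.887 | 8.2% |
| 0.26 | 0.6 | 18.757 | 13.328 | 0.843 | 9.9% |

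**Simulation of the width.** With 84 per arm, 5 imputations and ρ from 0.3 to 0.6, the SE ratio was 0.92-0.94 and the type I error 6.5-6.9% at 11% missing; at 26% missing they were 0.84-0.88 and 7.9-9.8%. Another simulation, just past the trigger at 11%, gave 5.6-7.0%. These agree with the formula.

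**Simulation of the remedy and of bias.** 80 against 80 patients, five visits, ρ = 0.5, true effect −1 NRS point. The arm effect was estimated from patient means, which on completed balanced data equals the random-intercept model. In the last four rows, scores after the first visit go missing according to the first pain score, with a dependence that differs by arm.

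| Missingness | Imputations | Other visits used | Bias | SE ratio | 95% coverage |
|---|---|---|---|---|---|
| Completely at random, 15% | 5 | no | 0.000 | 0.93 | 93.1% |
| Same | 5 | yes | −0.001 | 1.01 | 94.6% |
| Completely at random, 25% | 5 | no | 0.003 | 0.86 | 90.6% |
| Same | 5 | yes | 0.003 | 1.01 | 95.4% |
| Completely at random, 25% | 40 | no | −0.014 | 0.88 | 91.8% |
| By first score in one arm, 16% | 5 | no | 0.203 | 0.93 | 87.1% |
| Same | 5 | yes | −0.004 | 1.00 | 95.3% |
| By first score, opposite in the two arms, 19% | 5 | no | 0.407 | 0.91 | 69.9% |
| Same | 5 | yes | 0.014 | 1.00 | 95.5% |

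Going from 5 to 40 imputations leaves the SE ratio at 0.88, so the predictor set is the cause.

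**Mixed model without imputation.** In another simulation (85 per arm, SD 2, ρ = 0.6, missingness depending on pain in one arm only), a true −1.0 came out as −0.74 with 76% coverage under inclusion-only imputation, and as −0.99 with 95% coverage from the mixed model on observed visits.

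**The case against.** **What stands against the point.** The rule operates only above 10% missing. The protocol expects at most 5% missing for the primary endpoint and gives no rate for effort pain, so the rule may never be used. Patients do arrive in intensive care under propofol sedation, which makes gaps at H3 and H6 plausible but does not establish a rate. That effort pain belongs to the hierarchy is inferred from the order of the Statistical analysis text. Just past the trigger the inflation is modest. The test is confirmatory only after both QoR-15 comparisons at H24 succeed, so the primary conclusion is untouched. Bias needs a particular missingness pattern; there is none when scores are missing completely at random.

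**What does not rescue the rule.** The complete-case and best-worst analyses sit beside the imputed main analysis and do not correct its standard error. Chained equations can use other incomplete variables, but the plan names inclusion variables as the predictors, and the natural reading is that these are the whole set.

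**Stronger readings that the documents do not support.**

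- *Five imputations make the interval too narrow, or let the result be chosen by seed.* The first is ruled out by the 40-imputation run. As to the second, the seed is pre-specified. A small number only adds Monte Carlo noise.
- *The arm is left out of the imputation model, so effects shrink.* Follow-up says "Once the patient is included and allocated to one arm, the block will be carried out", and a reader might take allocation as coming after inclusion. Both occur at the end of surgery, and no text excludes the arm. It deserves naming, no more.
- *Imputing QoR-15 corrects nothing.* Pre-operative QoR-15 is collected before surgery and is not an analysis covariate, so imputing from it adds information and can correct missingness related to it. Nor is the interval of this single-time endpoint narrowed.
- *All pain scores are affected.* Pain at rest is not imputed.

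**Conclusion.** The point holds for effort pain up to H48. If more than 10% of these scores are missing and the plan is followed as written, the confidence interval for the visit-averaged arm effect is too narrow. Under five visits, correlation 0.3 to 0.6 and scores missing completely at random, the real type I error of a nominal 5% test is about 6-7% at 11% missing and 8-10% at 26%. The narrowing was also seen under an unstructured covariance. Where missingness depended on earlier pain differently by arm, a true effect of −1.0 was biased by +0.20 to +0.41; this size belongs to the assumed patterns and should not be read as a forecast.

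The same reasoning applies to the mixed model for morphine-equivalent consumption, but that case was not simulated. The conclusion rests on effort pain being a hierarchy endpoint, which the text supports but the missing figure would have to confirm.

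**What to change.** Before unblinding, replace the parenthesis that fixes the predictors:

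1. For hierarchy endpoints analysed by a mixed model (effort pain, morphine-equivalent consumption), do not impute. Fit the model to all observed visits and state that this is valid under missing at random.
2. For QoR-15 at H24 and H48, if more than 10% are missing, name arm and stratum explicitly as predictors, keep pre-operative QoR-15, and add QoR-15 at the other post-operative times with the pain and opioid data. Follow-up already schedules the later scores: "The QoR-15 questionnaire will be completed at H48 and H72". This gains information and protects against missingness related to post-randomization data; it does not correct an error.
3. Optionally raise the number of imputations, for example to 50, to reduce Monte Carlo noise.

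The cost is a sentence or two in the analysis plan and a few minutes of computing. The variables are already collected, and neither the sample size nor trial conduct changes.

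### The best-worst and worst-best checks push missing patients in every arm the same way, so on continuous endpoints they move the group difference only by the imbalance in missingness times one SD

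*Protocol article*

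**What the plan says.** The missing-data paragraph of the protocol article (Statistical analysis) covers endpoints in the type I error hierarchy. Up to 10% missing, nothing is imputed. Above that, multiple imputation from variables at inclusion is used, and its influence is then examined: "If the multiple imputation method is used (i.e., more than 10% missing data), we will study the impact of the data imputation". That examination has an analysis of the available cases and two scenarios labelled best-worst and worst-best.

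The scenarios are defined in one sentence. The best-worst half reads "it is assumed that all patients lost to follow-up will have a beneficial outcome, whereas in the", and the sentence then turns to the second label, under which the same patients are all given the opposite result: "scenario, they will have a negative outcome". For continuous endpoints the good value is fixed first: "the beneficial outcome will be the mean value of the group plus one standard deviation". The bad value mirrors it: "while the adverse outcome will be the mean minus one standard deviation". Neither sentence separates the arms, and no other section restates or corrects the rule.

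**The concern.** A paired label such as best-worst conventionally means that missing patients in one arm get the good outcome and those in the comparator get the bad one. Worst-best swaps the arms. The two scenarios then bracket how far informative missingness could push the treatment difference. The definition given here applies one direction to everyone, so the label and the definition describe different analyses.

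This matters because the imputation model uses only variables at inclusion and so assumes data missing at random given baseline. The same paragraph allows that data may be missing non-randomly, and these two scenarios are the only stated analyses that depart from the missing-at-random assumption. The primary endpoint is a paper questionnaire that patients fill in themselves in the ICU at 24 hours, so a link between poor recovery and non-completion is plausible. If the scenarios return nearly the observed difference whatever the missing patients were like, a reader may take that as evidence of robustness.

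**Working it through.** **Inputs from the Sample size section.** SD 18 and standard-group mean 90: "the average FQoR-15 score was 90 ± 18". Block means: "we set mean QoR-15 values of 98 in the SPIP group and 106 in the DPIP group". The planned differences are therefore 106 − 98 = 8 for DPIP versus SPIP, and (98 + 106)/2 − 90 = 12 for combined blocks versus standard. The article gives only two missing-data figures, a planning maximum of 5% and the 10% trigger. All other missing rates below are assumptions.

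**The plan's own figure.** n per group = 2 × (1.960 + 0.842)² × 18² / 8² ≈ 79.5, so 80. This reproduces the stated 80 and confirms that SD 18 and a difference of 8 are the working assumptions.

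**Effect of the rule.** If a fraction m of an arm is missing and filled with that arm's mean ± SD, the arm mean moves by ± m × SD. For two arms with fractions m1 and m0, the size of the shift in the difference is:

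- same direction in both arms (as written): |m1 − m0| × SD
- opposite directions: (m1 + m0) × SD

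| Missing, arm 1 / arm 0 (assumed) | Shift as written | Shift, opposite directions |
|---|---|---|
| 11% / 11% | 0.0 | 0.22 × 18 = 3.96 |
| 12% / 12% | 0.0 | 0.24 × 18 = 4.32 |
| 15% / 15% | 0.0 | 0.30 × 18 = 5.4 |
| 20% / 20% | 0.0 | 0.40 × 18 = 7.2 |
| 15% / 9% | 0.06 × 18 = 1.08 | 0.24 × 18 = 4.32 |
| 20% / 10% | 0.10 × 18 = 1.8 | 0.30 × 18 = 5.4 |
| 20% / 5% | 0.15 × 18 = 2.7 | 0.25 × 18 = 4.5 |

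**DPIP versus SPIP, observed difference 8.** The smallest significant difference is about 1.96 × 18 × √(2/80) = 5.58. At 12% per arm, the unfavourable opposite-direction scenario gives 8 − 4.32 = 3.68, which is not significant. As written, the difference stays at 8.0.

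Pooled t-tests with 84 per arm, filled-in values included and missing counts rounded to whole patients, give:

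| Missing per arm | As written | Opposite, unfavourable |
|---|---|---|
| 11% | 8.0, p ≈ 0.004 | 4.14, p = 0.14 |
| 15% | 8.0, p ≈ 0.004 | 2.43, p = 0.38 |
| 20% | 8.0, p ≈ 0.004 | 0.71, p = 0.79 |

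As written, the test even looks slightly stronger than with the available cases, because constants are added. At 11% missing (9 of 84 per arm) the standard error falls from 18 × √(2/75) = 2.94 to 2.76, so t rises from 8/2.94 = 2.72 to 8/2.76 = 2.90.

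**Combined blocks versus standard, observed difference 12.** Opposite directions, unfavourable scenario: about 8.1 (p = 0.0008) at 11%, 6.6 (p = 0.006) at 15% and 4.8 (p = 0.04) at 20%.

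**Alternative reading of the group.** If the group meant the pooled sample, both arms would receive the same value and the difference would shrink by the missing fraction: 8 × (1 − 0.12) = 7.04 at 12% per arm. Neither reading produces opposing directions.

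**The case against.** The strongest reply concerns weight. The scenarios run only for hierarchy endpoints with more than 10% missing, and the article plans for at most 5% missing on the primary endpoint. On its own assumption they would never be run for QoR-15 at 24 hours. When run, they are secondary checks on the imputation. The labels also suggest that the authors meant the conventional version, so this may be a slip in condensing a fuller document, and an analyst might follow the label. All of this stands and limits the importance of the point. It does not remove it: the published rule is explicit down to the filled-in value, and it contradicts its own labels.

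A reader might infer that the scenarios cannot test robustness at all. The documents do not support that. The zero shift needs equal missing fractions. At an assumed 20% versus 5%, the written rule can take 8 points to 5.3 by the formula (5.2, p = 0.06, with whole patients), which loses significance. Nor does the formula carry over to binary endpoints. There, giving every missing patient the same result shrinks the risk difference by the factor 1 − m under balanced missingness, so it does move.

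The article also plans an available-case analysis, a classification of the missingness mechanism and a per-protocol analysis. The imputed result would therefore not stand unchecked, but none of these replaces a scenario for non-random missingness with opposing directions.

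**Conclusion.** The definition conflicts with its labels and, followed literally, gives a weak check. On continuous endpoints the difference moves only by the imbalance in missingness times one SD, and not at all under balance. At an assumed 12% per arm and SD 18, this is 0.0 points against 4.3 for opposite directions, and 4.3 is 54% of the 8-point difference on which the DPIP versus SPIP comparison is sized.

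The consequence is largest for DPIP versus SPIP, the second step of the hierarchy. There a genuine opposite-direction scenario would remove significance from an observed 8 points. That is a loss of significance and not a change of sign. It would be wrong to infer that the trial's first conclusion hangs on this: with the planned 12 points, combined blocks versus standard stays significant even under opposite directions at about 11 to 15% missing.

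The primary estimate, the hierarchy and the sample size are untouched. The figures rest on SD 18, observed differences equal to the planned ones, and assumed missing rates above the trigger.

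**What to change.** Define the scenarios by arm for each contrast in the hierarchy:

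- **Best-worst:** the beneficial value for missing patients in the first-named arm (combined blocks; DPIP) and the adverse value in the comparator (standard; SPIP).
- **Worst-best:** the reverse.

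State the beneficial direction for each endpoint. For QoR-15 it is the group mean plus one SD. Where higher is worse, such as pain or morphine consumption if these are in the hierarchy, it is the mean minus one SD. The current text calls the higher value beneficial for every continuous outcome. For binary endpoints, say whether the event or its absence is the good outcome.

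The cost is a rewording of the two defining sentences plus a short list of directions by endpoint. No extra data are needed, and the sample size does not change. It should be settled before the unblinded analysis.
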